**1. Background**

Laparoscopic cholecystectomy is widely used in clinical practice due to its minimal trauma and rapid postoperative recovery. The gallbladder and biliary tract are areas densely innervated by the vagus nerve. During surgery, stimulation, traction, and dissection of the gallbladder or exploration of the common bile duct can cause biliary-cardiac reflex, leading to reflex coronary artery spasm, myocardial ischemia, cardiac function suppression, bradycardia, arrhythmia, and in severe cases, cardiac arrest. Previous literature reports that the incidence of circulatory arrest during biliary surgery is 3.07 times that of non-biliary surgery, with an occurrence rate of biliary-cardiac reflex ranging from 30% to 75%. Therefore, exploring an appropriate anesthesia management strategy to prevent biliary-cardiac reflex is crucial for the prognosis of patients undergoing laparoscopic cholecystectomy. Administering a low dose of esketamine after anesthesia induction, utilizing its sympathetic stimulation effect to raise blood pressure, increase heart rate, and suppress adverse reflexes, may help counteract vagal reflexes during cholecystectomy. Esketamine is the right-handed isomer of ketamine, exhibiting similar pharmacological characteristics by blocking NMDA receptors for analgesic effects. It has twice the affinity for NMDA receptors as racemic ketamine, with no difference in onset and duration of action but higher bioavailability and shorter half-life. In the nervous system, NMDA receptors are involved in pain signal transmission and amplification. Inflammatory factors released from tissue injury or stimulation increase NMDA receptor activity, leading to pain signal transmission and amplification. Hence, inhibiting NMDA receptor activity can alleviate pain perception. Therefore, we investigated the effect of low-dose esketamine on biliary-cardiac reflex during cholecystectomy and postoperative pain.

- 1. **Primary Objective**

To observe the effect of administering low-dose esketamine after anesthesia induction on biliary-cardiac reflex and postoperative pain during cholecystectomy.

- 1. **Secondary Objectives**

1. The incidence of adverse reactions to perioperative use of esketamine.
2. The effects of perioperative esketamine use on postoperative depression, anxiety, and cognitive function in patients.

**3. Study Design**

**3.1 Study Nature**

This is a prospective, single-center, double-blind, randomized controlled trial assessing the impact of esketamine on biliary-cardiac reflex and postoperative pain in patients scheduled for elective laparoscopic cholecystectomy.

**3.2 Sample Size Calculation**

Based on pre-experiment and literature reports, it is estimated that the incidence of biliary-cardiac reflex during surgery is 40% in the saline group. Assuming a 25% reduction in the incidence of biliary-cardiac reflex in the esketamine group, setting α=0.05 for a two-sided test and β=10%, PASS software calculations require 124 patients in total, equally divided into experimental and control groups. Considering a potential dropout rate of 20%, a total of 148 patients will be recruited.

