**3.3 Randomization and Blinding**

Patients will be randomized into two groups: control group C and experimental group K using the Research Randomizer website. The results will be stored in opaque envelopes, managed by a researcher not involved in patient recruitment, data collection, perioperative management, or postoperative follow-up. Before surgery, the coordinator will prepare the drugs according to the randomization results and provide them to the anesthesiologist responsible, labeled as "research drug" with the patient's random number. The anesthesiologists, surgeons, nurses, and follow-up personnel involved in the trial will be blinded to the group assignments until the end of the trial when all data have been recorded and analyzed.

**Emergency Unblinding:** In case of emergencies requiring knowledge of the treatment received, the principal investigator can decide to open the envelope to reveal the group assignment. Once opened, the case will be considered a dropout, and the reason recorded. The patient will not be included in efficacy analysis but will be included in adverse reaction analysis. If more than 20% of the envelopes are opened, the double-blind trial will be invalidated.

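### Recruiting 148 does not leave the required 124 patients after the stated 20% dropout; it leaves about 118

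*Protocol*

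**What the plan says.** Everything at issue is in section 3.2 of the protocol. It assumes that "the incidence of biliary-cardiac reflex during surgery is 40% in the saline group", continues with "Assuming a 25% reduction in the incidence of biliary-cardiac reflex in the esketamine group", and sets a two-sided 5% significance level and 10% type II error, that is, 90% power. From these inputs, "PASS software calculations require 124 patients in total, equally divided into experimental and control groups". The recruitment total follows: "Considering a potential dropout rate of 20%, a total of 148 patients will be recruited". No inflation formula is given.

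Section 3.3 bears on what a dropout means here. A patient whose envelope is opened in an emergency counts as a dropout, and "The patient will not be included in efficacy analysis but will be included in adverse reaction analysis". Section 4.3 lists further grounds for withdrawal (serious adverse events, protocol violations, patient request, loss to follow-up without efficacy data). It does not say whether withdrawn patients stay in the analysis.

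**The concern.** A dropout rate is a share of the patients recruited. To have 124 left after losing a fifth, the target must be divided by 0.80. Adding a fifth of the target to the target gives a smaller number, and 148 looks like the result of that shortcut.

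At stake is whether the plan delivers what it claims. Section 3.2 makes three linked statements: 124 patients are needed for 90% power, 20% may be lost, and 148 will be recruited. If the first two are taken at face value, the third is too small. The sample size paragraph is normally carried into the trial report, where any reader can see that 148 less 20% is not 124.

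**Working it through.** **Inputs (all from section 3.2).** Control incidence 40%; a 25% reduction; two-sided α = 0.05; power 90%; equal groups; 124 required; 20% dropout; 148 recruited.

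**Step 1: reproduce 124.** Read the reduction as 25 percentage points, so 40% against 15%. The two-proportion Z-test with unpooled variance gives

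n per arm = (z₀.₉₇₅ + z₀.₉₀)² × [p₁(1 − p₁) + p₂(1 − p₂)] / (p₁ − p₂)²

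= (1.960 + 1.282)² × (0.40 × 0.60 + 0.15 × 0.85) / 0.25²

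= 10.507 × 0.3675 / 0.0625 = 61.8, rounded up to 62.

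Two arms make 124, an exact match. Other two-sided formulas at 90% power give totals of 130 (pooled), 128 (arcsine) and 146 (continuity-corrected). A relative reduction of 25% (40% to 30%) needs 946 with the unpooled formula, so it cannot be the source of 124. The base figure therefore stands, and the fault lies in the dropout step alone.

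**Step 2: trace 148.**

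- 124 × 1.2 = 148.8, which gives 148 if truncated.
- 124 / (1 − 0.20) = 155, or 156 (78 per arm) to keep the groups equal.

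Only the first leads to 148. Rounding cannot explain the second, since 148 is 7 below 155.

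**Step 3: what 148 delivers.**

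- After 20% loss: 148 × 0.80 = 118.4, so about 118 patients, 59 per arm. Shortfall: 124 − 118 = 6.
- Largest loss that still leaves 124: (148 − 124) / 148 = 24/148 = 16.2%.

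**Step 4: effect on power (40% against 15%, two-sided 0.05).** With the unpooled formula, power = Φ(0.25 / √(0.3675/n) − 1.960):

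- n = 62: Φ(3.247 − 1.960) = 90.1%
- n = 59: Φ(3.168 − 1.960) = 88.6%
- n = 74 (nobody lost): Φ(3.548 − 1.960) = 94.4%

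The same comparison under other methods separates the cost of the dropout step from the choice of test:

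| Method | 59 per arm | 62 per arm | Loss (points) | 74 per arm |
|---|---|---|---|---|
| Unpooled Z (reproduces 124) | 88.6% | 90.1% | 1.5 | 94.4% |
| Pooled Z | 87.0% | 88.6% | 1.6 | 93.4% |
| Chi-square, exact enumeration | 88.0% | 89.1% | 1.2 | 93.8% |
| Fisher's exact test | 82.8% | 85.1% | 2.3 | 91.1% |

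Losses are taken from unrounded power values. Below the first row, part of the distance to 90% is already there at 62 per arm. It comes from the test, not from the dropout allowance.

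**The case against.** The best case for leaving the text alone is that the error hardly matters.

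- **Timing of the endpoint.** The reflex is observed during gallbladder manipulation (section 5.1), in the same operation in which the study drug is given before skin incision (section 3.4). Loss to follow-up at 24 to 72 hours cannot remove that outcome, so 20% loss is unlikely for the endpoint behind the sample size. If every dosed patient were analysed, 74 per arm would exceed 90% power under all four methods. This largely stands, with a limit: section 3.3 takes unblinded patients out of the efficacy analysis and section 4.3 leaves the fate of withdrawn patients open, so the loss need not be zero. Postoperative pain, also part of the primary objective, is assessed up to 72 hours and is exposed to later losses.
- **Size.** Like for like, the cost is about 1.5 points of power. Uncertainty in the control rate, for which section 1 cites 30% to 75%, matters more than three patients per arm. This stands. It would also be unfair to set 82.8% under Fisher's test against the stated 90%, because that test gives only 85.1% at the full 62 per arm.
- **The formula is inferred.** The protocol does not print 124 × 1.2, and 148.8 would usually be rounded up. This is true, but the shortfall does not depend on it: 148 less 20% is 118 however 148 was obtained.

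These points limit the consequence. None of them reconciles the three figures, and no other section does so.

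**Conclusion.** The concern holds. On the protocol's own figures, recruiting 148 with 20% dropout leaves about 118 evaluable patients, 6 short of 124; 155 (156 for equal arms) would be needed, and 148 tolerates at most 16.2% loss. With the formula that reproduces 124, power at the stated dropout is 88.6% rather than 90.1%.

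The shortfall in numbers is plain arithmetic and needs no assumption beyond dropout being a share of those recruited. The power figures rest on reading the 25% reduction as percentage points (40% to 15%), which the protocol does not spell out but which is the only reading compatible with 124. They also assume that dropouts contribute nothing to the efficacy analysis and are split evenly between the arms.

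This is a definite error in a stated design figure with a small effect. It should be corrected, but it does not threaten the trial.

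**What to change.** Keep 148 and correct the dropout sentence in section 3.2 in one of two ways:

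- 148 recruited patients provide 124 evaluable patients as long as dropout does not exceed 16%; or
- 148 recruited patients with 20% dropout provide about 118 evaluable patients (59 per arm) and about 88% power for 40% against 15%.

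It would help to add that the reflex endpoint is recorded within the same operation as dosing, so that if all dosed patients are analysed, 74 per arm gives about 93–94% power by the Z-test formulas (91% with Fisher's exact test). That addition is valid only if it is squared with the exclusion of unblinded patients in section 3.3.

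The cost is one sentence and a slightly less favourable stated dropout tolerance or power; no extra patients are needed. If the sponsor prefers to keep both 20% dropout and 90% power as stated, the recruitment total becomes 156 (78 per arm), 8 more than planned.

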**3.3 Randomization and Blinding**

Patients will be randomized into two groups: control group C and experimental group K using the Research Randomizer website. The results will be stored in opaque envelopes, managed by a researcher not involved in patient recruitment, data collection, perioperative management, or postoperative follow-up. Before surgery, the coordinator will prepare the drugs according to the randomization results and provide them to the anesthesiologist responsible, labeled as "research drug" with the patient's random number. The anesthesiologists, surgeons, nurses, and follow-up personnel involved in the trial will be blinded to the group assignments until the end of the trial when all data have been recorded and analyzed.

**Emergency Unblinding:** In case of emergencies requiring knowledge of the treatment received, the principal investigator can decide to open the envelope to reveal the group assignment. Once opened, the case will be considered a dropout, and the reason recorded. The patient will not be included in efficacy analysis but will be included in adverse reaction analysis. If more than 20% of the envelopes are opened, the double-blind trial will be invalidated.

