4.3 Withdrawal Criteria

Occurrence of serious adverse events.

Protocol violations (e.g., unexpected ICU transfer, poor patient compliance).

Patient request to withdraw.

Loss to follow-up with no efficacy data collected.

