5.1 Study Flow

Obtain written informed consent from patients before surgery, screen according to inclusion/exclusion criteria, and randomize using the randomization website. Store the randomization numbers in opaque envelopes. Preoperatively, introduce patients to the use of the Visual Analog Scale (VAS) for pain, the Hospital Anxiety and Depression Scale (HAD), and the Mini-Mental State Examination (MMSE).

All patients will undergo general anesthesia with intubation using a video laryngoscope, and be monitored using a Chinese multifunctional monitor for invasive arterial pressure, heart rate, SpO2, temperature, and end-tidal CO2. Anesthesia will be induced with propofol (2-3 mg/kg), rocuronium (0.6-1 mg/kg), and sufentanil (0.25-0.5 µg/kg). After loss of consciousness (absence of corneal and eyelid reflexes), tracheal intubation will be performed. Anesthesia will be maintained with remifentanil (0.1-0.3 µg/kg/min), propofol (3-4 mg/kg/h), and sevoflurane (0.7-1.0 MAC), with dosage adjusted by the anesthesiologist.

Definition of Biliary-Cardiac Reflex: During gallbladder manipulation or traction, if heart rate decreases (HR < 60 bpm) or drops by ≥20% from baseline along with a ≥20% drop in blood pressure from baseline, it will be classified as a biliary-cardiac reflex. If reflex occurs, surgery will be paused, and 0.5 mg of atropine will be administered intravenously. If recovery is not achieved quickly, the operation will be stopped, and rescue medications such as ephedrine, isoproterenol, or epinephrine will be administered.

Surgery will be performed by the same team of surgeons. Sevoflurane will be stopped 30 minutes before the expected end of surgery, and propofol and remifentanil infusions will be stopped at the end of the surgery. Patients will be observed for half an hour in the operating room after waking and restoration of spontaneous breathing before being transferred to the ward.

Postoperative Rescue Analgesia: Sufentanil will be titrated for analgesia. If VAS score > 3 (moderate to severe pain) or upon patient request, rescue analgesia will be administered and recorded. If VAS score ≤ 3 or if there is no request, no additional analgesia will be provided.

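### Excluding every code-broken patient from the efficacy analysis is a post-randomisation exclusion that can selectively remove main-outcome events

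*Protocol*

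**What the plan says.** Section 3.3 (Emergency Unblinding) sets the trigger: "In case of emergencies requiring knowledge of the treatment received, the principal investigator can decide to open the envelope to reveal the group assignment". It then fixes the consequence: "Once opened, the case will be considered a dropout, and the reason recorded", followed by "The patient will not be included in efficacy analysis but will be included in adverse reaction analysis". The only stated limit on how often this may happen is "If more than 20% of the envelopes are opened, the double-blind trial will be invalidated".

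The reflex is the main efficacy outcome by inference. The protocol names no single primary endpoint, but the primary objective reads "To observe the effect of administering low-dose esketamine after anesthesia induction on biliary-cardiac reflex and postoperative pain during cholecystectomy", and section 3.2 sizes the trial on reflex incidence alone.

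The Background describes the possible consequences of the reflex as including "bradycardia, arrhythmia, and in severe cases, cardiac arrest". Section 5.1 foresees a reflex that does not settle: "If recovery is not achieved quickly, the operation will be stopped, and rescue medications such as ephedrine, isoproterenol, or epinephrine will be administered". Section 4.3 separately lists "Occurrence of serious adverse events" and unexpected ICU transfer among the withdrawal criteria, without saying what happens to data already collected.

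Nothing in the protocol brings these patients back through an all-randomised or intention-to-treat analysis.

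**The concern.** The order of events matters. Under section 3.4 the drug is given once, before skin incision. Under section 5.1 the reflex is defined during gallbladder manipulation or traction. If the code is broken because of a severe reflex, the patient has already been dosed and the efficacy event has already been observed. Breaking the code afterwards cannot invalidate that observation, yet the rule takes it out of the efficacy comparison and leaves it only among the adverse reactions.

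Whether a patient is excluded can therefore depend on the outcome and, through reactions to the drug, on treatment. The bias has no fixed direction:

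- Losing reflex cases mainly from the saline arm hides benefit.
- Losing reflex cases mainly from the esketamine arm exaggerates benefit.
- Losing esketamine patients who had a drug reaction but no reflex raises that arm's reflex rate and hides benefit.

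This is not a detail that can be left to a statistical analysis plan, because the protocol itself states the exclusion. A plan that kept these patients would contradict it.

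**Working it through.** **Inputs.** Section 3.2: saline rate 40%, a 25% reduction, two-sided α = 0.05, β = 10%, 124 patients in two equal groups, 148 recruited. Section 3.3: 20% envelope limit. The share *s* of reflex cases that are unblinded and dropped is not in the protocol; every value of *s* below is an assumption.

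**Reproducing the plan's figure.** Reading the reduction as 25 percentage points (40% vs 15%), with a normal approximation and unpooled variance:

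n per arm = (1.960 + 1.282)² × (0.40×0.60 + 0.15×0.85) / 0.25² = 10.51 × 0.3675 / 0.0625 = 61.8, so 62 per arm and 124 in total.

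This matches. A relative reading (40% vs 30%) would need 946 in total by the same formula, so 40% vs 15% is the planned contrast.

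**Effect of the rule.** If a share *s* of an arm's reflex cases is removed, the observed rate is p(1 − s)/(1 − ps). For the saline arm at s = 0.20: 0.40×0.80/(1 − 0.08) = 34.8%. For the esketamine arm: 0.15×0.80/(1 − 0.03) = 12.4%.

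| s | Saline | Esketamine | Difference, both arms | Saline arm only | Esketamine arm only |
|---|---|---|---|---|---|
| 0 | 40.0% | 15.0% | 25.0 | 25.0 | 25.0 |
| 10% | 37.5% | 13.7% | 23.8 | 22.5 | 26.3 |
| 20% | 34.8% | 12.4% | 22.4 | 19.8 | 27.6 |
| 30% | 31.8% | 11.0% | 20.8 | 16.8 | 29.0 |

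Differences are in percentage points. In the last two columns the other arm stays at its true rate (for example 34.8 − 15.0 = 19.8 and 40.0 − 12.4 = 27.6).

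**Power.** With 62 per arm before exclusions and the pooled formula, power is 88.6% with no exclusion. (The pooled formula is slightly stricter than the unpooled one that yields 124.)

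- Removal in both arms at s = 10%, 20%, 30%: 85.9%, 82.5%, 78.2%.
- Removal in the saline arm only: 81.3%, 71.1%, 57.8%.

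**False positives.** Suppose there is no true effect (40% in both arms) and reflex cases are removed from one arm only. The chance of a significant result favouring that arm is 2.5% with no removal. It rises to 4.7%, 8.4% and 14.7% at s = 10%, 20% and 30%. One-arm removal is a limiting case.

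**Small numbers of code breaks.** With 74 per arm, 0.40 × 74 = 29.6 saline reflex cases are expected.

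- Dropping one: 28.6/73 = 39.2%, difference 24.2 points.
- Dropping two: 27.6/72 = 38.3%, difference 23.3 points.

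**Does the 20% limit protect?** With reflex cases removed at share *s* in both arms, the excluded share of all patients is s × (0.40 + 0.15)/2 = 0.275s. At s = 20% this is 5.5%, about 8 of 148. If only reflex cases are unblinded, the limit is reached only when s = 0.20/0.275, about 73% of all reflex cases.

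**The case against.** The strongest reply is that a reflex need not lead to a code break at all. Section 3.3 confines unblinding to emergencies in which knowledge of the treatment is needed, and leaves the decision to the principal investigator. Section 5.1 sets out a response to the reflex that is the same in both arms and does not refer to allocation. The definition also admits fairly mild falls in heart rate, so many of the expected 40% would not be emergencies. With 74 per arm about 41 reflex cases are expected (29.6 + 11.1 = 40.7), so s = 10% already means about four emergency code breaks and s = 30% about twelve. The true number may be lower. The decision to open the envelope also precedes knowledge of the arm, so purely one-arm removal is unlikely. Finally, the excluded patients are still reported among the adverse reactions.

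All of this stands, and it limits the size of the problem. It does not justify the rule: keeping an event in the safety tables does not restore the randomised efficacy comparison.

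Two stronger readings are tempting and should be resisted. A reader might infer that the rule deletes the most severe reflex cases as a matter of course. The protocol does not say so; it can delete them, and some code breaks will have other causes. A reader might also note that 20% of 148 envelopes (29.6) equals the reflex count expected in the saline arm (0.40 × 74 = 29.6) and conclude that the plan tolerates losing all of them. That is a numerical coincidence. The 20% is a limit for invalidating the trial, not an expected rate, and the match would require every saline reflex to be unblinded and nobody else.

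**Conclusion.** The point holds in this form: section 3.3 fixes a post-randomisation exclusion that can depend on outcome and treatment, no other part of the protocol reverses it, and the 20% limit is no safeguard against it. The size is unknown because no unblinding rate is given. Under the planned 40% vs 15%, the bias is about one point for a single lost saline reflex. It is 1.2 to 4.2 points if 10% to 30% of reflex cases are lost in both arms, and 2.5 to 8.2 points if they are lost from the saline arm only. Removal confined to the esketamine arm would inflate the difference instead, by 1.3 to 4.0 points. If code breaks are few, the bias is small. The conclusion treats the reflex as the main outcome, as inferred from the primary objective and the sample size.

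**What to change.** In section 3.3, delete the statement that an opened case is a dropout and the sentence that excludes it from the efficacy analysis. Replace them with wording such as:

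*Patients whose code is broken remain in the efficacy analysis in their randomised group, with the biliary-cardiac reflex as observed. Assessment of pain and other follow-up continues where consent allows. The time of and reason for unblinding are recorded. An analysis without these patients is a sensitivity analysis only.*

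In section 4.3, add that withdrawal, including after a serious adverse event or unexpected ICU transfer, does not remove outcomes already observed from the efficacy analysis. Without this, the same patients could be lost by a second route.

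The cost is protocol wording, plus continued follow-up of a few patients for the 24, 48 and 72 hour pain scores in section 5.2. The reflex itself is already recorded, so that outcome needs no new data. The change does not affect when the code may be broken or how any patient is managed. One small downside is that pain scores after unblinding may be influenced by knowledge of allocation; the sensitivity analysis addresses this.
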